## Abstract

**Objectives:**

The COVID-19 pandemic has been a significant stressor worldwide and reports of psychological distress, depression, sedentary lifestyles, and overall decreased wellbeing are increasing. Yoga practices have been found to improve mental and physical health. The purpose of this randomized controlled trial is to compare Isha yoga practitioners to controls on perceived stress, resilience, wellbeing, and protection and recovery from COVID-19. Trial Design. In this prospective randomized control trial, the effects of yoga practices are being compared between seasoned yoga practitioners with two controls who are age (±3 years), gender matched, and living in the same neighborhood.

**Methods:**

Participants will be asked to complete a series of web-based surveys at baseline, six weeks, and 12 weeks. These surveys include validated scales and objective questions on COVID-19 infection and medical history. The validated questionnaires assess stress, mood states, resilience, and overall wellbeing. Questionnaires, weekly activity diaries, and medical history, will be collected using REDCap.

**Results:**

We hypothesize that routine yoga practice during the COVID-19 pandemic will reduce stress, enhance well-being, and provide protective effects against COVID-19.

**Conclusion:**

With the growing concern about the physical and mental impacts of COVID-19 and increased interest in alternative practices such as yogic practices, this study will contribute to the growing body of evidence about the safety and efficacy of yoga for emotional, mental, and physical health conditions.

## Introduction

1

With nearly 82 million cases and 1.8 million deaths worldwide as of the end of December 2020 [1], the COVID-19 pandemic has been a significant stressor worldwide. The severity of the disease and dearth of definitive treatments has led to thousands of deaths each day. Our understanding of the pandemic's effects on individuals, families, and communities as well as our methods of coping continue to evolve. Measures such as social distancing and working remotely have been enforced worldwide to curb disease transmission. This has led to an increased number of people staying indoors, living a more sedentary lifestyle, and greater feelings of isolation [2]. Additionally, reports of psychological distress [3,4], anxiety [5], sleep disturbances [6], and problematic substance use have increased [7]. In the U.S., the COVID-19 pandemic is exacerbating the opioid epidemic and has led to a dramatic increase in overdose deaths [8]. Clinicians and public health professionals have stressed the importance of maintaining good mental, emotional, and physical health during these turbulent times [9,10].

Yoga practices, which include specific breathing, meditation, and posture protocols, can enhance physical and mental well-being [11,12]. Research demonstrates that regular yoga practice can modulate the autonomic nervous system [13], improve sleep quality [14], boost immunity [15] and reduce stress [16], anxiety [17,18], and depression [19]. Regular yoga practice also has demonstrated neuroprotective effects [20] as well as benefits for cardiac autonomic control and breathing function [21]. In addition to these well-being indicators, there is some evidence that yoga practices can improve immune, lung, and respiratory function and enhance anti-inflammatory response – important factors for COVID-19 protection and recovery. In two systematic reviews of yoga and asthma, researchers found some evidence that yogic practices can reduce medication usage and improve symptoms [22,23]. In a study of respiratory illnesses, the meditation group compared to two control groups (exercise or no intervention), was found to suffer less severe symptoms [24]. Similarly, Barrett et al. [25], sought to investigate potential preventive effects of meditation or exercise on incidence, duration, and severity of acute respiratory infection (ARI) illness. They found that compared to the control or exercise groups, illness duration, number of days-of-work missed, and illness severity was less for the meditation group.

Yoga can be practiced by anyone, requires no infrastructure, and is a restorative, individual activity easily performed during periods of social distancing. Public interest in yoga practices is increasing and often touted in media outlets as a means of coping with stress and improving health [[26], [27], [28]]. The Centers for Disease Control and Prevention reports that between 2012 and 2017, the number of adults practicing yoga or meditation rose from 9.5% to 14.3%, and 4.1% to 14.2 respectively [29]. More rigorous research is needed to better understand how yoga may play a role in improving mental and physical well-being in the general population.

## **Objectives.** The purpose of this randomized controlled trial is to accomplish the following specific aims

**2**

Specific Aim 1: To quantitatively assess the effects of Isha yoga practices between seasoned practitioners and control groups on perceived stress, resilience, and wellbeing by use of validated scales.

Specific Aim 2: To compare protection and recovery from COVID-19 infection between seasoned Isha yoga practitioners and controls as demonstrated by:a.Self-reported duration of fever and respiratory symptoms in COVID-19 positive participantsb.Self-reported readiness to return to work (or a feeling of being physically and mentally fit)

Specific Aim 3: To compare prevalence rates of diagnosed COVID-19 infection between the seasoned Isha yoga practitioners and age and gender matched controls at baseline, 6 weeks and 12 weeks.

We hypothesize that routine yoga practice during the COVID-19 pandemic will reduce stress and enhance well-being.

## Materials and methods

3

### Participant recruitment

3.1

We will employ a two-stage recruitment design. First, seasoned yoga participants will be recruited by social media, websites, flyers, word of mouth, email announcements at the Isha Foundation [30], an international school of yoga. Seasoned yoga participants are defined as individuals who have completed at least one, in-person yoga Isha Yoga training protocol with an Isha yoga trainer and are regularly doing the practice. The Isha Foundation will facilitate this stage of the recruitment by including study recruitment flyers and links to its broad follower base of meditators and yoga practitioners. These communications will have a survey link where prospective participants can confirm their interest in the study and learn more detailed information about study procedures. They will then be directed to a brief REDCap survey where they will be asked screening questions to ensure study eligibility. Those who are eligible will be directed to an electronic consent form and enrolled in the study following the submission of the consent agreement.

The second stage of the recruitment uses snow-ball sampling [31]. Following enrollment in the study, seasoned yoga practitioners are requested to nominate two friends who can act as age and gender matched controls, preferably living in the same neighborhood. The study team will reach out to the nominated individuals to describe the study, assess interest and eligibility, and direct prospective respondents to an electronic consent form specific for the control groups. Respondents will be enrolled following the provision of their consent.

The process of nominating controls for the study is voluntary and seasoned yoga practitioners can participate without referring any controls. In this situation, unmatched controls and practitioners will be matched by the study team based on their self-reported location details. The team prioritizes matching the zip codes followed by town, city, county, and state.

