### Intervention description and timing

3.2

This is analytic study wherein an observational arm of ‘seasoned yoga practitioners’ is being compared with age, gender, and region matched ‘non-meditators’ as controls. The non-meditators control group is further randomized to active comparator arm and placebo comparator arm.

Control participants or Non-meditators are individuals with minimum (<1 month) to no yoga practice of any kind, prior to study enrollment. Non-meditator controls randomized to an ‘Active comparator arm’ are taught a 3 min yoga practice (Simha Kriya) which involves deep breathing exercises and meditation following randomization. Within the yogic tradition, there are breathing exercises which are considered to foster pranayama, which builds a type of “armor” or Kavacham for oneself against negative impacts encountered in the every day world. Prana is considered the fundamental energy and the foundation for all life. Pranayanic practices have been shown to contribute to positive physiologic and psychologic changes including improvements in hypertension, cognitive function, breathing frequency, stress, and heart rate variability [13,[32], [33], [34]]. In a study of another Isha pranayama practice, Peterson et al. found that after 6 weeks of daily practice, participants reported improved general well-being (General Well-Being Scale) and lower levels of perceived stress (Perceived Stress Scale) [35]. In the current study, the Simha Kriya practice will be taught on-line by highly-trained Isha practitioners and participants are asked to perform Simha Kriya using a web-based application, twice per day.

The other control group acts as a ‘Placebo comparator arm’ and performs either reading activities or remaining idle for 15 min a day throughout the study period. Respondents in the observational arm (seasoned yoga practitioners) continue their usual yoga practices. Please see Fig. 1 for study flow chart. Participants aged <18 years or >80 years will excluded from the study. Please see Table 1 for additional Inclusion/Exclusion Criteria.

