Aim 2 Analysis. To Compare Protection and Recovery from COVID 19 infection between seasoned Isha yoga practitioners and controls as demonstrated by:a.Self-reported duration of fever and respiratory symptoms in COVID-19 positive participantsb.Self-reported readiness to return to work (or a feeling of being physically and mentally fit)

We will calculate the protection and recovery rates from COVID-19 infection as defined by the aforementioned criteria. Given the continuous nature of the criteria used to assess symptom duration and sense of recovery, differences between groups will be assessed in a univariable manner with a parametric or non-parametric *t*-test. We will perform spot analysis at the three defined points to capture the point prevalence of recovery rates. We also intend to assess the differences between the prevention and recovery rates at baseline and six weeks and baseline and twelve weeks. We will employ the mixed model technique similarly to the analysis suggested in the aim #1 analysis.

Analysis of Aim 3: To compare Prevalence rates of diagnosed COVID-19 infection between the seasoned Isha yoga practitioners and age and gender matched controls at baseline, 6 weeks, and 12 weeks.

We will compute period prevalence of diagnosed COVID-19 infections as a measure of frequency. Since the data to be analyzed are not dependent on duration, we intend to compute the prevalence rates at the following time points: baseline, 6 weeks, and 12 weeks. The result would be reported as the portion of study population with COVID-19 at the specified time point.

Finally, we will perform an exploratory analysis of the data collected by comparing the effect of yoga practices and their duration between the 3 study groups to estimate a dose-response trend if possible.

Compliance is defined as 3 days of activity each week for at least 3 weeks from baseline to 6 weeks, or a minimum of 6 weeks from baseline to 12 weeks. Measures of frequency and association will also be calculated. We will complete exploratory analysis by comparing the different yoga practices and their duration between the 3 study groups to assess a dose-response pattern.

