We hypothesize that routine yoga practice during the COVID-19 pandemic will reduce stress, enhance well-being, and provide protective effects against COVID-19. While a direct comparison between seasoned yoga practitioners and non-meditators at baseline would have been sufficient to establish the effectiveness of yoga practices; the dynamic progression of COVID in varying geographical regions at different rates warranted these comparisons at least at two other time points separated by 6 weeks each. Furthermore, by incorporating a robust short (3 min) breathing yoga activity into the non-meditator cohort in a randomized fashion, we aimed to establish that exposure to any yoga practice will significantly improve mental health status in non-meditators. With the growing concern about the physical and mental impacts of COVID-19 and increased interest in alternative practices such as yogic techniques, this study will contribute to the growing body of evidence about the safety and efficacy of yoga for emotional, mental, and physical health conditions.

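### Nominated controls enrol after their practitioner and nothing aligns survey dates, so the practitioner-versus-control comparisons may be made at different points in a moving epidemic

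*Protocol article*

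**What the plan says.** Recruitment has two stages (section 3.1). Practitioners are screened, consented and enrolled first. Then "The second stage of the recruitment uses snow-ball sampling": "Following enrollment in the study, seasoned yoga practitioners are requested to nominate two friends who can act as age and gender matched controls". The team contacts the nominees, checks interest and eligibility, and takes consent; "Respondents will be enrolled following the provision of their consent". Nominating is voluntary, and "seasoned yoga practitioners can participate without referring any controls", so no rule makes a practitioner wait for controls. People left without a match are paired by the team on reported location: "The team prioritizes matching the zip codes followed by town, city, county, and state". Section 3.2 says the practitioner arm "is being compared with age, gender, and region matched" with non-meditators. Enrolment date is not a matching variable in either section.

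Surveys are web-based and automated, at baseline, 6 and 12 weeks (section 3.3). In section 3.6 the time term of the mixed model is the visit, related subjects share a random intercept, and adjustment for confounders is optional. For Aim 3 the plan is to "compute the prevalence rates at the following time points: baseline, 6 weeks, and 12 weeks". The Discussion recognises that the epidemic moves and says that "the dynamic progression of COVID in varying geographical regions at different rates warranted these comparisons at least at two other time points".

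**The concern.** Diagnosed COVID-19, and plausibly perceived stress during a pandemic, depend on when a person is asked as well as on who is asked. If controls answer the baseline survey some weeks after the practitioners they are compared with, the epidemic has moved on in between. While diagnoses accumulate, the later group shows the higher prevalence even at identical risk, and that would be read as protection by yoga. When a wave is falling, a measure of recent infection moves the other way and could hide a real benefit. The practitioner-versus-control contrasts carry Aims 1 to 3, and the stated analysis has no step that separates a date difference from a yoga effect.

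**Working it through.** **Is there a lag, and which way does it run?**

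- *Nominated sets.* The practitioner enrols and then nominates. The friend is contacted, screened, consented and enrolled. The friend's enrolment cannot come before the practitioner's, so the lag has one direction.
- *Team-made sets.* Pairing uses location, within the age, gender and region matching of section 3.2. A control already enrolled may be paired with a practitioner who joins later, or the reverse. The lag can take either sign and has no stated limit.
- *Survey clock.* The article does not say when each clock starts. Consent-then-enrol, automated surveys and the absence of a waiting rule or common survey date all suggest a clock for each person. This is an inference.

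**Does the stated analysis remove it?**

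- The visit indicator measures study time. Two people at week 6 have the same value whatever the date.
- The random intercept models similarity within a cluster. It does not remove a date difference between the practitioner and the control inside that cluster.
- Location matching deals with differences between regions, not with different dates in one region.
- Later visits do not help. If a control starts L weeks after the practitioner, the gap at week 6 is (L + 6) − 6 = L, and at week 12 it is (L + 12) − 12 = L.

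**How large could it be?** The article gives no lag, growth rate, sample size or expected prevalence, so there is no figure to reproduce. Everything below is assumed, with no true effect of yoga.

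*Cumulative prevalence*, growing by a proportion g per week: control/practitioner ratio = (1 + g)^L.

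| Lag L | g = 5% | g = 10% |
|---|---|---|
| 1 week | 1.05 | 1.10 |
| 2 weeks | 1.05² = 1.10 | 1.10² = 1.21 |
| 4 weeks | 1.05⁴ = 1.22 | 1.10⁴ = 1.46 |

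For example, 4.0% in practitioners becomes 4.0% × 1.22 = 4.9% to 4.0% × 1.464 = 5.9% in controls at four weeks.

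*Incidence in windows of equal length*, with weekly incidence multiplied by r each week: ratio = r^L. At four weeks, r = 1.10 gives 1.46 and r = 0.90 gives 0.90⁴ = 0.66. The direction depends on the phase of the epidemic.

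*Perceived stress*, with an assumed drift of 0.25 points per week, SD 7 and 150 per group: shift = 0.25 × L, standard error = 7 × √(2/150) = 0.81. At two weeks the shift is 0.5 points, with about a 9% chance of a significant difference in the direction of the drift. At four weeks it is 1.0 point, with about 24%. With no drift that chance is 2.5%, half of the two-sided 0.05.

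**The case against.** The strongest reply is that the key step is inferred. The article never says that each clock starts at that person's consent, and neither the study flow chart nor the full protocol is at hand. Consent is electronic, so the lag may be days. At one week the assumed ratio is only 1.05 to 1.10. Section 3.6 also allows regression on confounders that differ between groups, and survey date could be one of them. Finally, the remark in the Discussion is mainly about regional variation, which location matching addresses.

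Much of this stands, and it limits the claim. A reader might infer that controls as a whole are surveyed later and that the trial is therefore biased towards yoga. The text does not support that. The one-way lag holds only within nominated sets, team-made sets can lag either way, and the share of each is not given. Nor can a large distortion be claimed without the lag. The size and direction for symptom duration among infected participants (Aim 2) have not been shown, and the ratios above do not apply to that outcome.

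The optional adjustment does not answer the point, because it is not a commitment and names no date term. The point is also more than missing detail. The article states a comparison of prevalence at study visits, and a calendar-aligned comparison is better and cheap. The Discussion does not claim that repeated visits cure an enrolment lag, but it offers them as the response to a moving epidemic, and they cannot align the groups.

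**Conclusion.** The point holds as a conditional design weakness. Enrolment order and matching allow practitioner and control surveys to fall on different dates, and the stated analysis would not correct for it. It rests on the inference that survey clocks run from each person's own enrolment. The bias is of unknown size and sign: small if the lag is about a week or less, and material for Aim 3 if it reaches several weeks in a fast-moving period. It concerns only the practitioner-versus-control contrasts, which are observational. The contrast of Simha Kriya with reading/idle is unaffected, because both arms come from the same stream of controls and are block randomised (section 3.5). The point should be addressed, but it does not by itself invalidate the study.

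**What to change.** 1. From the REDCap survey dates, report the distribution of dates by group and the lag within matched sets, separately for nominated and team-made sets. If the lag is short, this may largely settle the matter.
2. Adjust the practitioner-versus-control models for calendar date of survey, for example by month or a spline, by region. The adjustment relies on overlap in dates between the groups, which step 1 will show.
3. For Aim 3, compare diagnosed infection over the calendar interval that matched members share. This needs the date of diagnosis, and the article does not say whether that is asked.
4. Say in the Discussion that repeated study-time points do not align the groups in calendar time.

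The cost is a few extra model terms and some follow-up lost from the shared interval: with a four-week lag, 12 − 4 = 8 weeks remain in common. A prospective enrolment window would come too late, since section 3.6 reports that the 12-week data have already been reviewed. No retrospective re-matching is needed. For the same reason, the date-adjusted results should be labelled as added after data review.

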### Intervention description and timing

3.2

This is analytic study wherein an observational arm of ‘seasoned yoga practitioners’ is being compared with age, gender, and region matched ‘non-meditators’ as controls. The non-meditators control group is further randomized to active comparator arm and placebo comparator arm.

Control participants or Non-meditators are individuals with minimum (<1 month) to no yoga practice of any kind, prior to study enrollment. Non-meditator controls randomized to an ‘Active comparator arm’ are taught a 3 min yoga practice (Simha Kriya) which involves deep breathing exercises and meditation following randomization. Within the yogic tradition, there are breathing exercises which are considered to foster pranayama, which builds a type of “armor” or Kavacham for oneself against negative impacts encountered in the every day world. Prana is considered the fundamental energy and the foundation for all life. Pranayanic practices have been shown to contribute to positive physiologic and psychologic changes including improvements in hypertension, cognitive function, breathing frequency, stress, and heart rate variability [13,[32], [33], [34]]. In a study of another Isha pranayama practice, Peterson et al. found that after 6 weeks of daily practice, participants reported improved general well-being (General Well-Being Scale) and lower levels of perceived stress (Perceived Stress Scale) [35]. In the current study, the Simha Kriya practice will be taught on-line by highly-trained Isha practitioners and participants are asked to perform Simha Kriya using a web-based application, twice per day.

The other control group acts as a ‘Placebo comparator arm’ and performs either reading activities or remaining idle for 15 min a day throughout the study period. Respondents in the observational arm (seasoned yoga practitioners) continue their usual yoga practices. Please see Fig. 1 for study flow chart. Participants aged <18 years or >80 years will excluded from the study. Please see Table 1 for additional Inclusion/Exclusion Criteria.

**Fig. 1 fig1:**
[figure not shown]
Study flow chart.

**Table 1 tbl1:** Inclusion and exclusion criteria.

	Inclusion	Exclusion
Seasoned Yoga Practitioners	Must be an Isha School of Yoga practitioner	
	Must have completed Inner Engineering Online course and practice Shabhavi Mahamudra Kriya or Shakthi Chalan Kriya	
		Participants <18 years of age
		Participant >80 years of age
		Participants must be able to read and understand English.
Control groups	Must have little to no experience with Isha school of yoga	
	Should have practiced yoga routinely for <1 Month (if previously experienced in yoga)	
		Participants < 18 years of age
		Participant > 80 years of age
		Participants must be able to read and understand English.

